#### Budget Impact Analysis (BIA)

A BIA will be performed according to the ISPOR principles of Good Practice for Budget Impact Analysis. This BIA allows prediction of the financial consequences related to the adaption and implementation of the genotype guided dosing strategy in severely depressed patients, in order to determine the affordability of the intervention. Data will be used that reflect the size and characteristics of the depressed population in the Netherlands together with the results of this trial (effect sizes, resource use etc). When relevant, budget impact analyses are generated as a series of scenario analyses.

### 6.4 Withdrawal of individual subjects

Subjects can leave the study at any time for any reason if they wish to do so without any consequences. The investigator can decide to withdraw a subject from the study for urgent medical reasons.

#### 6.4.1 Specific criteria for withdrawal (if applicable)

Criteria for withdrawal are:

1. when, according to the treating physician, a different biological treatment than TCA-pharmacotherapy is urgently needed (for instance electroconvulsive therapy (ECT) in case of active suicidal behaviour) .
2. Intolerable adverse reactions.
3. Severely decreasing somatic condition
4. Allergic reactions.

**6.5 Replacement of individual subjects after withdrawal**

Patients will not be replaced as withdrawal is accounted for in the estimation of the number of subjects necessary for screening.

**6.6 Follow-up of subjects withdrawn from treatment**

The data of withdrawn patients will be included in the analyses based on the intention-to-treat model. If possible we will keep withdrawn patients in the study for the part of the economic evaluations.

**6.7 Premature termination of the study not applicable.**

Not applicable.

## 7. SAFETY REPORTING

This study is not evaluating the TCAs per se, but we have decided to apply the safety regulations for AEs and SAEs that are common in clinical trials.

### 7.1 Temporary halt for reasons of subject safety

In accordance to section 10, subsection 4, of the WMO, the sponsor will suspend the study if there is sufficient ground that continuation of the study will jeopardise subject health or safety. The sponsor will notify the accredited METC without undue delay of a temporary halt including the reason for such an action. The study will be suspended pending a further positive decision by the accredited METC. The investigator will take care that all subjects are kept informed.

### 7.2 AEs, SAEs and SUSARs

#### 7.2.1 Adverse events (AEs)

Adverse events are defined as any undesirable experience occurring to a subject during the study, whether or not considered related to [the investigational product / trial procedure/ the experimental intervention]. All adverse events reported spontaneously by the subject or observed by the investigator or his staff will be recorded.

#### 7.2.2 Serious adverse events (SAEs)

A serious adverse event is any untoward medical occurrence or effect that

- results in death;
- is life threatening (at the time of the event);
- requires hospitalisation or prolongation of existing inpatients' hospitalisation;
- results in persistent or significant disability or incapacity;
- is a congenital anomaly or birth defect; or
- any other important medical event that did not result in any of the outcomes listed above due to medical or surgical intervention but could have been based upon appropriate judgement by the investigator.

An elective hospital admission will not be considered as a serious adverse event.

The investigator will report all SAEs to the sponsor without undue delay after obtaining knowledge of the events.

The sponsor will report the SAEs through the web portal *ToetsingOnline* to the accredited METC that approved the protocol, within 7 days of first knowledge for SAEs that result in death or are life threatening followed by a period of maximum of 8 days to complete the initial preliminary report. All other SAEs will be reported within a period of maximum 15 days after the sponsor has first knowledge of the serious adverse events.

**Suspected unexpected serious adverse reactions (SUSARs):** not applicable

### **7.3 Annual safety report**

not applicable.

### **7.4 Follow-up of adverse events**

All AEs will be followed until they have abated, or until a stable situation has been reached. Depending on the event, follow up may require additional tests or medical procedures as indicated, and/or referral to the general physician or a medical specialist. SAEs need to be reported till end of study within the Netherlands, as defined in the protocol

### **7.5 [Data Safety Monitoring Board (DSMB) / Safety Committee]**

We do not expect that patients in this study are exposed to extra risks besides the risks of venepuncture. Instead we expect lower risk levels (see Summary section, paragraph on Burden and Risks, and see the following paragraph 11 on Structured risk analysis). A DSMB is not needed in this study.

## 8. STATISTICAL ANALYSIS

DATA-ANALYSIS Patient characteristics will be summarized as means or percentages depending on the type of measurement. All analyses are performed according to an intention-to-treat principle.

### 8.1 Primary study parameter(s)

For the measurement of differences in the primary study parameter (time needed to reach a plasma level in the therapeutic range) we will report survival probabilities according to the Kaplan-Meier method together with 95% confidence intervals (CIs). Results will be compared using two-sided log-rank test statistics. Median survival times (MST) will be presented. Patients who have not reached the study endpoint after 7 weeks will be censored to the time point of their most recent plasma level assessment.

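### Censoring patients who stop TCA treatment or withdraw makes week-7 attainment and median times look better than they are in both arms, and leaves the earliest leavers out of every log-rank risk set

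*Protocol*

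**What the plan says.** The primary outcome is time to a steady-state TCA level within the therapeutic range, over seven weeks of treatment (sections 6.1.1 and 6.3). Section 8.1 plans Kaplan-Meier estimates with confidence intervals and median times, and says "Results will be compared using two-sided log-rank test statistics". Its one censoring rule reads: "Patients who have not reached the study endpoint after 7 weeks will be censored to the time point of their most recent plasma level assessment".

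Section 6.4.1 lists the criteria for withdrawal. They include "Intolerable adverse reactions" and the situation in which "a different biological treatment than TCA-pharmacotherapy is urgently needed"; the others are severe somatic decline and allergic reactions.

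On what happens next, section 6.6 says "The data of withdrawn patients will be included in the analyses based on the intention-to-treat model" and adds: "If possible we will keep withdrawn patients in the study for the part of the economic evaluations". No further plasma levels are planned. Section 8 opens with the general statement "All analyses are performed according to an intention-to-treat principle".

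The first steady-state level comes at different times. In control the dose is built up during week 1 and the level follows 7 days later (section 3, Strategy 2). In intervention it comes 7 days after the last dose change (Strategy 1). Before that, only the level 12 hours after the first dose exists (section 6.3).

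**The concern.** Kaplan-Meier censoring assumes that a censored patient would go on to attain at the same rate as those who remain. A patient who has stopped the TCA because of intolerance, or been moved to another treatment, will generally not attain a therapeutic level of it. The planned curve therefore describes a hypothetical trial without withdrawal. A reader will take its week-7 percentage and median as what randomised patients experienced.

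A patient who leaves before any steady-state level is censored at the 12-hour level, before an event is possible, and so contributes nothing to the log-rank test. This happens in both arms, over a longer window in control.

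At stake are the reported attainment figures and whether a difference in withdrawal between the strategies can be seen at all.

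**Working it through.** **Inputs.** Medians of 4 weeks (control) and 2 weeks (intervention), two-sided 5% alpha, 80% power and 44 per group come from section 2.4; 100 per arm from sections 2.4 and 6.2; 7 weeks from sections 6.3 and 8.1. The withdrawal rate is an assumption. The allowance from 250 to 200 patients pools drop-out before treatment with loss to follow-up and gives no on-treatment rate.

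**Step 1: the plan's own figure.** With exponential times the hazard ratio is 4/2 = 2. Freedman's formula gives (1.960 + 0.842)² × ((2 + 1)/(2 − 1))² = 7.849 × 9 = 70.6, so 71 events. Week-7 attainment is 1 − 0.5^(7/4) = 0.703 and 1 − 0.5^(7/2) = 0.912, mean 0.807. Then 71/0.807 = 88 in total, or 44 per group. The stated figure reproduces.

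**Step 2: Kaplan-Meier against actual attainment.** Let h = ln 2 / median be the weekly attainment rate and w = −ln(1 − W)/7 the weekly withdrawal rate. W is latent withdrawal: the share that would withdraw by week 7 if attainment did not come first. Rates are taken as constant and independent.

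- Kaplan-Meier: 1 − exp(−7h).
- Cumulative incidence: h/(h + w) × [1 − exp(−7(h + w))].
- Median from cumulative incidence: −ln[1 − 0.5(h + w)/h] / (h + w).

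Example, control, W = 20%: h = 0.1733, w = 0.0319, h + w = 0.2052. Cumulative incidence = 0.8446 × (1 − exp(−1.436)) = 0.644, against 0.703.

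| W | Control: KM | Control: actual | Median (weeks) | Intervention: KM | Intervention: actual | Median (weeks) |
|---|---|---|---|---|---|---|
| 5% | 70.3% | 68.8% | 4.08 | 91.2% | 89.7% | 2.02 |
| 10% | 70.3% | 67.4% | 4.16 | 91.2% | 88.2% | 2.04 |
| 20% | 70.3% | 64.4% | 4.37 | 91.2% | 85.1% | 2.09 |
| 30% | 70.3% | 61.2% | 4.64 | 91.2% | 81.8% | 2.14 |

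The overstatement is about 1.5, 3, 6 and 9 points in either arm. Latent withdrawal of 30% corresponds to 18% of controls actually leaving before attainment. At w = 0.08 per week, 26% of controls leave, actual attainment is 56.8% and the median is 5.18 weeks.

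**Step 3: patients with no steady-state level.** The share leaving before the first level is 1 − (1 − W)^(2/7) in control (day 14) and 1 − (1 − W)^(1/7) in intervention (day 7, dose unchanged). For W = 20% this is 6.2% and 3.1%; for W = 30%, 9.7% and 5.0%.

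**Step 4: effect on the comparison.** A simulation used weekly visits, 100 per arm, the plan's medians, first levels at weeks 2 and 1, and 1,500 runs.

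| Latent withdrawal, control / intervention | Planned rule: mean z (power) | Kept as not attained to week 7: mean z (power) |
|---|---|---|
| 30% / 30% | 4.52 (99.5%) | 4.02 (97.5%) |
| 30% / 10% | 4.61 (99.9%) | 5.46 (100%) |
| 10% / 30% | 4.71 (99.9%) | 3.11 (88.2%) |

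The planned test barely moves with which arm withdraws more. The alternative moves a good deal, in either direction.

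**The case against.** **The rule does not name withdrawal, and such detail belongs in a SAP.** It is true that withdrawal is not named. But section 8.1 states a rule that covers everyone without the endpoint, and nothing else covers withdrawn patients. The point concerns what that text fixes, not something left out.

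**Censoring is compatible with intention to treat.** Largely so: patients stay in their allocated arm and their observed time counts. A reader might infer an outright contradiction, but sections 6.6 and 8 do not prescribe competing-risk handling. What stands is narrower: patients without a steady-state level are nominally included but inform no comparison.

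**The direction between arms is unknown.** This stands. A reader might infer that withdrawals are commoner in control and that the rule hides a real benefit. The trial's hypothesis concerns side effects, while the withdrawal reasons also include need for another treatment, somatic decline and allergy. Early intervention leavers are dropped too.

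**Power is not the problem.** This also stands at the plan's hazard ratio of 2. At an assumed ratio of 1.5 with withdrawal of 0.02 (control) and 0.05 (intervention) per week, power is about 68% with censoring and about 36% with withdrawn patients retained, so retention is not a general gain.

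**Replacing the log-rank test changes the question.** It does. With equal attainment speed and more withdrawal in control (0.05 or 0.08 against 0.02 per week), the retained comparison rejects in about 10% to 23% of runs, because it responds to withdrawal. The objective is faster attainment, so the log-rank test can stay.

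**Conclusion.** The point holds for the reported estimates. Week-7 attainment and median times are overstated in both arms whenever withdrawal ends TCA treatment. The direction is certain; the size is about 1.5 to 9 points for assumed latent withdrawal of 5% to 30%, with constant and independent rates. The control median moves from 4 weeks to between 4.08 and 4.64 over the same range.

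It holds in a limited form for the comparison: the earliest leavers enter no risk set, and a difference in withdrawal between arms is invisible whichever way it runs. The documents do not support reading this as a bias for or against the intervention, as an error in the sample size, or as a material loss of power at the planned effect.

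**What to change.** In section 8.1:

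1. Report cumulative incidence of attainment by arm with 95% confidence intervals for all randomised patients, with stopping TCA or withdrawal before attainment as a competing event. Take the attainment percentages and medians from it.
2. Keep the planned log-rank test as the test of attainment speed.
3. Pre-specify a supplementary comparison in which withdrawn patients are kept as not attained to day 49 (Gray's test).
4. Tabulate withdrawals by arm and reason, so that the two comparisons can be read together.

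The cost is a change of wording and some extra analysis; no treatment or data collection changes. The attainment figures will look less favourable. The supplementary comparison mixes attainment speed with withdrawal, so it may weaken or strengthen the result depending on which arm withdraws more, and should be labelled that way.

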### 8.2 Secondary study parameter(s)

The secondary continuous outcomes will be analysed by either student's t-test or Mann Withney U test dependent on the normal distribution of data or not. For the HAM-D scores we will compute the reduction as the baseline scores minus the scores at 7 weeks of treatment. FIBSER scores for side effects will be reported as means and standard deviations; qualitative details of the side effects will also be provided. For all statistical test we will use a significance level of 5% (two-sided). For missing values we will use the most recent HAM-D score that is available before the end of the medication study (7 weeks). For the FIBSER we will use the highest level of side effects measured during the medication study.

In additional analyses we will compare the primary and secondary outcome measures of the deviant metabolizer groups with those of patients with the normal metabolism phenotype.

Multiple regression analysis will be used to study the predictive effects of the early TCA serum/plasma level and other clinical (psychomotor retardation) and biological factors on the primary and secondary outcome measures (see research questions).

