### 2.4 Sample size calculation

#### SAMPLE SIZE CALCULATION

Based on clinical guidelines and experience, we designed a survival model according to which 50% (median survival) of the control group reaches steady state concentrations within the therapeutic range at 4 weeks. We assume that 50% of the intervention group will reach steady state concentrations within the therapeutic range at a maximum of 2 weeks. This difference of only 2 weeks is a conservative estimate as patients in the intervention group may immediately start at an optimal dose based on pharmacogenetic testing results. Taking an alpha level of 5%, two-sided tests of significance and a power of 80%, the model predicts a sample size of 44 patients per group. An essential condition imposed by the subsidising party (ZonMW) was that the sample size should be enough to answer two of the secondary research questions (regarding depression scores and side effects) as well. For both of the secondary measures we need 63 patients per group based on a reduction of the mean level of side effects (Frequency, Intensity, and Burden of Side Effects Rating FIBSER (Wisniewski et al. 2006)) from 2.98 (sd=1.88) to 2.04 (based on Star-d study results) For depression scores we expect a mean HAM-D reduction in the intervention group of 17.5 (sd=9) points compared to 13 points in controls (adapted from the DUDG study Wijkstra et al. 2010). To account for drop-out before treatment initiation and loss to follow-up we aim to include 250 patients, resulting in 100 patients in each arm

The sample size calculation for this study was performed by a statistician of the Department of Health Evidence, Radboudumc ([name]).

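### Carrying the last HAM-D score forward to week 7 biases the arm comparison when dropout differs by arm, and shrinks a real effect even when dropout is equal

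*Protocol*

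**What the plan says.** Section 8.2 of the Protocol fixes three things for HAM-D.

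- **Outcome:** the baseline score minus the week-7 score.
- **Test:** "The secondary continuous outcomes will be analysed by either student's t-test or Mann Withney U test dependent on the normal distribution of data or not".
- **Missing scores:** "For missing values we will use the most recent HAM-D score that is available before the end of the medication study (7 weeks").

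The schedule in section 6.3 marks HAM-D and QIDS at baseline and at every weekly visit to week 7. Section 8.2 names no arm comparison of HAM-D that uses the weekly course. A mixed repeated-measures analysis appears only in section 8.3, for the economic evaluation.

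Section 6.4.1 lists intolerable adverse reactions and the urgent need for a different biological treatment among the reasons for withdrawal. The burden-and-risk paragraph of the Summary expects fewer side effects in the intervention arm. Section 6.6 includes the data of withdrawn patients under intention to treat and adds: "If possible we will keep withdrawn patients in the study for the part of the economic evaluations".

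HAM-D is a secondary outcome, but section 2.4 reports that the funder required a sample large enough to answer it. The planning figures are: "we expect a mean HAM-D reduction in the intervention group of 17.5 (sd=9) points compared to 13 points in controls".

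**The concern.** Carrying a score forward treats the last value before dropout as if it had been observed at week 7. In a population that improves over the seven weeks, this understates the reduction of each patient who leaves. If the arms lose different numbers of patients, or lose them at different times, the understatement does not cancel and a difference can appear without any effect on mood.

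Unequal dropout is plausible on the trial's own reasoning: patients are withdrawn for intolerable reactions, and such reactions are expected to be fewer with genotype-guided dosing. A difference in tolerability could then be read as a difference in depression scores, although the protocol poses these as two separate secondary questions.

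This is not a detail left to a later plan. The protocol states the rule, while also scheduling the weekly scores that would make it unnecessary.

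**Working it through.** **Inputs from the Protocol.** Mean HAM-D reduction 17.5 against 13, SD 9, two-sided 5%, power 80%, 63 per group (section 2.4); 100 per arm (sections 2.4 and 6.2); weekly HAM-D to week 7 (section 6.3).

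**Assumptions, not in the Protocol.** Mean improvement is linear over seven weeks. The last observed visit of a dropout is uniform over weeks 1 to 6. A dropout would otherwise have followed the mean course of the arm. Dropout percentages by arm are chosen for illustration.

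**1. The plan's own figure.** n per group = 2 × (1.96 + 0.842)² × (9/4.5)² = 62.8, so 63. The stated figure reproduces. With 100 per arm and complete data, power for 4.5 points is 94%.

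**2. Loss per dropout.** A patient last seen in week k is credited with k/7 of the full reduction. The mean fraction lost over k = 1 to 6 is (6+5+4+3+2+1)/(6 × 7) = 0.5. For a 13-point reduction this is 6.5 points.

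**3. No true difference (13 points in both arms).** Bias = (control dropout − intervention dropout) × 6.5. The standard error is 9 × √(2/100) = 1.27. The rejection rate is P(|Z + bias/1.27| > 1.96).

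| Dropout, control / intervention | Spurious difference | Share of planned 4.5 | Type I error |
|---|---|---|---|
| 20% / 20% | 0 | 0% | 5% |
| 15% / 10% | 0.33 | 7% | 5.7% |
| 20% / 10% | 0.65 | 14% | 8.0% |
| 30% / 10% | 1.30 | 29% | 17.5% |
| 10% / 30% | −1.30 | −29% | 17.5%, in favour of control |

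**4. True difference of 4.5 (17.5 against 13).** Expected estimate = 17.5 × (1 − 0.5 × intervention dropout) − 13 × (1 − 0.5 × control dropout).

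- 20% / 20%: 15.75 − 11.70 = 4.05
- 20% / 10%: 16.63 − 11.70 = 4.93
- 30% / 10%: 16.63 − 11.05 = 5.58
- 10% / 30%: 14.88 − 12.35 = 2.53

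**5. Simulation.** 3000 runs, 100 per arm, with further assumptions: SD of the reduction rising to 9 at week 7, AR(1) correlation of 0.8 between weeks, and dropout unrelated to the scores within each arm. With carry-forward and no true effect, type I error was 4.5% at 20/20%, 8.5% at 20/10%, 16.4% at 30/10% and 18.9% at 10/30%. With a true 4.5 and 10/30% dropout, power fell to 48%.

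A likelihood analysis of the same weekly scores gave estimates of −0.05 to 0.01 when the truth was 0 and 4.48 to 4.53 when it was 4.5. Rejection was 4.8 to 5.4% under no effect, and power 89 to 91%. These rates were standardised by the spread of the estimates across runs, so they show absence of bias rather than test a model-based standard error. The result also depends on dropout at random, which the simulation built in.

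**The case against.** **The size rests on dropout rates the protocol does not give.** This stands. Section 2.4 plans 250 inclusions to reach 200 patients, but that allowance mixes loss before treatment with loss to follow-up and is not split by arm. A 5-point imbalance adds less than one percentage point to the type I error.

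**The 6.5-point loss assumes that dropouts would have completed the full improvement.** This also stands. Patients who stop for intolerable reactions or urgent other treatment may not have done so. The figures measure bias against the difference had everyone continued.

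**A reader might infer that the bias favours the intervention.** The documents do not establish this. Fewer side effects with genotype guidance is a hypothesis under test. The reverse imbalance works against the intervention, and equal dropout dilutes a real effect.

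**Other readings go too far:**

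- The weekly scores are not simply thrown away, because they supply the carried-forward values.
- Section 6.6 does not say that withdrawn patients are kept only for the economic part. It states a hope for that part and is silent on continued HAM-D rating.
- An invalid standard error is not shown: simulated type I error was 4.5% at equal 20% dropout. The inflation comes from the shifted mean.
- No numerical harm has been shown from choosing the test on normality.
- Omitting baseline HAM-D and the stratification factors costs precision, not validity, and precision is ample with 100 per arm against 63 needed.

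None of this defends carry-forward itself. Under the assumptions above it is biased when dropout is unequal, and also at equal dropout when the effect is real.

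**Conclusion.** The point holds for the carry-forward rule as the main HAM-D analysis. In the scenarios with more dropout in control and no true effect, the spurious benefit ranges from 0.33 to 1.30 points. Equal 20% dropout takes about 10% off a true 4.5. All of this is conditional on linear improvement, uniform timing of dropout and the assumed rates. The direction in the actual trial cannot be told from the protocol.

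The primary log-rank analysis does not use these scores, and the sample size is correct as stated. Because HAM-D is secondary, this is a should-fix. It still deserves action because the sample size was required to answer this question and the data for a better analysis are already scheduled.

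**What to change.** In section 8.2:

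- Make the main analysis of HAM-D, and likewise QIDS-SR, a mixed model for repeated measures on all weekly scores. Include arm, week, arm-by-week, baseline score and the three stratification factors of section 6.2 (phenotype, drug, in- or outpatient status). Report the week-7 contrast with its 95% confidence interval.
- Remove the normality-dependent choice of test for these outcomes.
- Keep carry-forward at most as a sensitivity analysis, and add one for dropout that is not at random, for example reference-based imputation from the control course.
- State whether scores obtained after TCA is stopped count in the main analysis. Including them changes the quantity estimated, since they may reflect the response to another treatment. If they count, extend section 6.6 so that HAM-D and QIDS ratings continue to week 7 where the patient agrees.

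The cost is protocol wording and slightly more analysis work, plus some effort to keep rating patients who stop if those scores are to count. No visit, sample-size or treatment change is needed. The downside is that the main analysis then assumes missingness at random, which is why the second sensitivity analysis belongs with it. The change should be fixed before outcome data are seen.

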**Nature and extent of the burden and risks associated with participation, benefit and group relatedness:**

Overall, there will be a maximum of 4 extra blood withdrawals: one for the CYP450 genotyping, two samples for plasma storage (one at baseline and one after 7 weeks of treatment) and one for the 12 hours TCA serum/plasma level analysis at day 1 of treatment. The first sample will be taken together with the regular blood withdrawal for standard laboratory investigations. For the other samples extra venepunctures are necessary. If a patient prefers not to give blood for genetic testing we will isolate DNA from the saliva. In addition, the assessments necessary for cost effectiveness analysis will give extra burden (beyond standard high care). We do not expect that patients in this study are exposed to extra risk besides the risks of venepuncture. Instead we expect lower risk levels: in the intervention group the TCA doses are adjusted to the individual CYP450 phenotype based on the most actual KNMP guidelines and therefore we expect lower levels of side effects and earlier treatment response. The weekly monitoring for side effects and depressive symptoms in all participating patients give a low burden to the patients but contribute to extra safety compared to regular care. Our study is aimed at decreasing risk in the patients by lowering the chances for side effects and reducing the time to therapeutic response compared to treatment as usual.

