### Secondary Objectives:

- To assess whether genotype guided dosing results in lower rates of adverse effects compared to dosing as usual. .
- To assess whether genotype guided dosing results in earlier reductions of depressive symptoms compared to dosing as usual. .
- To assess the value of an early TCA serum/plasma level (12 hours after the first dose) as a potential predictor of time to therapeutic plasma concentration, treatment response and side effects.

- To explore the predictive value of other clinical (psychomotor retardation) and biological factors (measures of metabolomics) and the changes within these factors during treatment to therapeutic plasma concentration, treatment response and side effects.
- To compare the healthcare costs and work related costs of genotype based dosing to dosing as usual.

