## 6.2 Randomisation, blinding and treatment allocation

Randomization: 200 patients will be 1:1 randomized over the two different dosing strategies. We will use stratified block randomisation using the computer programme CASTOR ([nl.castoredc.com](http://nl.castoredc.com)). In order to make comparable groups, the stratification will take 1. CYP-based phenotype, 2. drug type (NOR vs.CLOMI vs.IMI), and 3. baseline patient status (inpatient vs. outpatient) into account (in this order). An exception to this randomization protocol is when a patient carries a deviant cytochrome P450 metabolism for both CYP2D6 and CYP2C19 while imipramine is prescribed. In this case, patients will be switched to nortriptyline and randomized accordingly. As the number of stratification variables should be limited to avoid empty cells, we will plan additional statistical adjustments for gender, age and sociocultural differences in case of imbalance between study groups.

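### The blanket uncorrected 5% level in section 8.2 also covers the metabolomics predictors and their changes; these tests need false-discovery control and a hypothesis-generating label

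*Protocol*

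**What the plan says.** - **Predictors.** The protocol's Secondary Objectives include this aim: "To explore the predictive value of other clinical (psychomotor retardation) and biological factors (measures of metabolomics) and the changes within these factors during treatment". The targets are the therapeutic concentration, treatment response and side effects.
- **Method.** Section 8.2: "Multiple regression analysis will be used to study the predictive effects of the early TCA serum/plasma level". The same sentence extends the method to psychomotor retardation and "biological factors on the primary and secondary outcome measures (see research questions". It names no form of regression and does not say whether factors are tested singly or together.
- **Error rate.** Section 8.2: "For all statistical test we will use a significance level of 5% (two-sided". No exception or multiplicity rule is stated.
- **Patients.** Section 6.2: "200 patients will be 1:1 randomized over the two different dosing strategies". The sample size section agrees: "we aim to include 250 patients, resulting in 100 patients in each arm".
- **Sampling.** The Summary's paragraph on burden and risks lists "two samples for plasma storage (one at baseline and one after 7 weeks of treatment", and the schedule in section 6.3 shows the same two time points. Each metabolite can therefore supply one baseline level and one change to week 7.
- **Panel size.** The number of metabolites is not stated.

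**The concern.** Metabolomics normally means many measured variables per sample, and here each can enter twice. A fixed 5% level per test, repeated over level, change and several outcomes, produces a predictable number of significant results when nothing is predictive. Section 8.2 gives the reader no means of separating these from real signals, because the metabolite tests share the threshold used for the treatment comparisons and carry no exploratory label there.

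The objective is also about predictive value. If many metabolites are put into one unpenalised model, the fit in the data that built it overstates how well it would predict in new patients.

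A third problem lies in timing. The change in a metabolite is known only at week 7, whereas the primary outcome is the time at which a therapeutic level is reached, with follow-up of 7 weeks. A change score used to predict that time is measured at or after the event.

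At stake is the credibility of the predictor findings. The treatment comparison and the sample size do not depend on them.

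**Working it through.** The protocol gives no predictor count, error rate or sample size for these regressions, so there is no figure of its own to reproduce. Its 44 and 63 patients per group concern the treatment comparisons and do not bear on this point.

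**Inputs from the protocol**
- Level per test: 0.05 two-sided (section 8.2).
- Patients: n = 200 at most (section 6.2).
- Terms per metabolite: 2, baseline level and change (Secondary Objectives; two plasma samples).
- Outcomes: 5 clinical ones in sections 6.1.1 and 6.1.2, namely time to level, HAM-D, QIDS-SR, ASEC and FIBSER.

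**Assumptions**
- Number of metabolites K: 10 to 100.
- Smaller analysed sample: n = 160, to allow for patients without a week-7 sample.

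**Step 1. Chance findings when each metabolite term is tested on each outcome**

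Expected number if no term is predictive = 2K × 5 × 0.05 = 0.5K. This expectation does not require independent tests; correlation changes only the spread around it.

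| K | Tests (2K × 5) | Expected significant by chance |
|---|---|---|
| 10 | 100 | 5 |
| 20 | 200 | 10 |
| 50 | 500 | 25 |
| 100 | 1,000 | 50 |

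The objective can also be read as three outcomes (time to level, response, side effects). The count is then 2K × 3 × 0.05 = 0.3K, or 3 to 30.

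For K = 10 baseline levels on a single outcome, the expected count is 10 × 0.05 = 0.5. If those tests were independent, the chance of at least one would be 1 − 0.95^10 = 40%.

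**Step 2. One unpenalised joint linear model per outcome**

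This is a separate scenario from step 1. Take p = 2K + 2 predictors, the two extra being the early TCA level and the retardation score. Residual degrees of freedom = n − 1 − p. Expected R-squared with no association = p/(n − 1).

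| K | p | Residual df, n = 200 | Null R-squared, n = 200 | Null R-squared, n = 160 |
|---|---|---|---|---|
| 10 | 22 | 177 | 22/199 = 0.11 | 22/159 = 0.14 |
| 20 | 42 | 157 | 42/199 = 0.21 | 42/159 = 0.26 |
| 50 | 102 | 97 | 102/199 = 0.51 | 102/159 = 0.64 |
| 100 | 202 | −3 | no unique fit | no unique fit |

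At p = 199 with n = 200 the parameters, counting the intercept, equal the patients. No residual degrees of freedom remain and no test is possible. Below that the model can be fitted but becomes imprecise: the power to detect a partial correlation of 0.2 with n = 200 is 80% at p = 10, 52% at p = 100 and 29% at p = 150.

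**Step 3. Timing of the change score**

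Under section 8.1, patients without the endpoint after 7 weeks are censored, so events are counted up to week 7. The second plasma sample is taken at week 7. The change is therefore never available before the event whose time it is meant to predict. The baseline level is.

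**The case against.** **The statistical analysis plan may settle this.** Panel size, choice of predictors and joint or separate modelling are proper matters for that plan, and their absence here is no fault. This part of the objection stands. The 5% level is different, because the protocol states it. The sentence sits among the secondary comparisons, but it says all tests, and no other level is given for the regressions. A later plan with false-discovery control would depart from it.

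**The aim is exploratory.** The objective is worded as exploration, no primary conclusion rests on it, and uncorrected exploratory testing is common when labelled. This lowers the weight of the point. The label is missing where the analysis is specified.

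**A reader might infer that the protocol prescribes ordinary least squares with every metabolite in one model.** It does not. It says multiple regression, a term that does not exclude a Cox or penalised model, and it does not say how metabolites enter.

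**A reader might infer that most significant metabolites would be false.** That depends on the share of true predictors and on power, neither of which the protocol gives. False positives outnumber true ones only if the true share is below 0.05/(0.05 + power): about 6% at 80% power, 9% at 50% and 14% at 30%.

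**A reader might infer that the regression cannot be run, or that it would always show a good fit.** With 10, 20 or 50 metabolites the joint model in step 2 can be fitted. Under the usual linear-model assumptions its overall F-test keeps its 5% error and the adjusted R-squared averages zero. Only the raw R-squared inflates, and the protocol does not say that it will be reported. R-squared from a linear model also does not apply to the censored primary outcome.

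**Conclusion.** The point holds in a limited form. Section 8.2 states an uncorrected 5% level for all tests, and these include metabolomics predictors and their changes on the primary and secondary outcomes, in at most 200 patients. If none were predictive, about 5 to 50 significant results would be expected by chance. That range assumes 10 to 100 metabolites, two terms each and five clinical outcomes; with three outcomes it is 3 to 30.

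Overfitting is conditional on a single unpenalised joint model. It is modest at 10 metabolites, severe at 50, and with level and change both entered the model has no unique fit at 100. The documents do not establish that such a model is intended, or that chance findings would be the majority.

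The timing problem needs no assumption about panel size: the change to week 7 cannot serve as a predictor of time to therapeutic level. The text should be corrected, but the primary treatment comparison is unaffected.

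**What to change.** In section 8.2:

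1. Exempt the metabolomics tests from the general 5% rule. Control the false discovery rate at a stated level across metabolites, terms and outcomes, and label the results hypothesis-generating.
2. If metabolites are modelled jointly for prediction, report internally validated performance, for example by cross-validation, instead of in-sample fit. A penalised model is one suitable choice but need not be mandatory.
3. For time to therapeutic level, name a censored-data model, such as Cox regression, and use baseline metabolites only.

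The change is to analysis wording and needs no extra patients, samples or visits. The downside is that fewer single metabolites will be called significant, so some weak true associations will be missed.
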